### 3.3 Clinical Evidence to Date

See chapter 3.1

### 3.4 Dose Rationale

n.a; the investigational products will be applied as per product information.

### 3.5 Explanation for choice of comparator

See chapter 3.1

### 3.6 Risks/Benefits of the study

All patients can witness adverse events related to surgical procedures and decolonization, which however, are related to the therapy itself, and not to the specific study protocol. A theoretical risk could be a higher incidence of SSI and related wound problems in the Non-Decolonization arm. Patients in the decolonization arm could witness more skin irritation, intolerance and allergy to octenidin and/or ingredients of the formulations. The potential benefits are a reduction of the SSI risk and related wound problems in the decolonization arm.

*Pregnancy and breast-feeding*

The use of topical formulations containing octenidin is not a known danger for the fetus and the breast-fed newborn. However, due to formality reasons inherent to most interventional trials, we exclude pregnant or breastfeeding women from the trial.

### 3.7 Justification of choice of study population

See chapter 3.1. No vulnerable participants are included.

## 4. STUDY OBJECTIVES

To reduce the incidence of SSI (and other unplanned postoperative wound revisions) in a highly selected patient population with an elevated risk for SSI. To show the safety and all potential (any) adverse events observed during the decolonization period and during the hospitalization for surgery.

## 5. STUDY OUTCOMES

### Primary outcomes:

- Remission (and inversely superficial or deep-space SSI and revision surgeries for non-infected wound problems; composite primary outcome) at 6 weeks (and/or a 1 year for surgeries with implant)

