The duration of pre-surgical decolonization is planned to be five days. However, when this pre-surgical time period is too short, the decolonization may also start at least 3 days before surgery and be continued up to 2 days post-surgery. During the post-surgery application, the patient will be washed with water and octenisan® by their treating nurses. The patient will also return the empty/used set and answer to a short questionnaire during their hospital stay. The study team will recuperate the questionnaire during hospitalization. We renounce on routine microbiological assessments of skin colonization, but the hospital's infection control can demand it for other reasons regarding infection control. Hence, skin colonization data will only be available for some selected patients that are screened for body carriage of antibiotic-resistant pathogens, according to the infection control recommendations in Switzerland.

There will be a Monitoring at study start, the interim analysis and at the end.

The primary study outcomes are unplanned revision surgery for SSI and wound problems at 42 days for all surgeries; or 1 year in case of an implant-related surgery. Secondary objectives are other unplanned revision surgeries for non-SSI reasons, all adverse events, as well as patient's subjective impression of the decolonization.

The treatment period includes the following daily study visits:

- Visit 1 - Enrollment (Day 1)
- End-of-Treatment (EOT) -Visit is the Day of Surgery or Day 1-2 after surgery
- Test-of-Cure-Visit (TOC) (clinical surgical control) - Day 42 (+/- 14 days)
- Further follow-up (eventually by phone call) for implant-related surgery - 1 year (+/- 2 months)

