#### 3.2.1 Study definitions

An orthopedic infection for this trial is the microbiological evidence of bacteria in at least two intraoperative tissue samples together with radiological (osteomyelitis, collections, inflammation) and/or clinical evidence of infection (pus, discharge, sinus tracts, rubor, calor, pain). Histological proof is facultative for this study. Implants are defined as any implants except for transient wires or fixator pins. A wound problem is any unplanned post-surgical wound pathology leading to surgical revision. Remission of infection is the absence of clinical and/or radiological and/or laboratory signs of (former) infection after the minimal follow-up time of 1 year for implant -related surgery with implants left in place; or two months for implant-free surgery (including surgery when all implants have been removed)..

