### 9. STUDY ASSESSMENTS

#### 9.1 Assessment of primary outcome

Judged by local wound healing (healed vs delayed wound healing according to Reference). The wound healing will be assessed visually by orthopaedic surgeons. Wound nurses and the study investigators may help in the assessment of wound problems, but in case of doubtful cases, the opinion of the treating physician will dominate the decision upon the presence or absence of wound problems and/or infection.

Persistent postsurgical pain, serum laboratory markers, or the patient's subjective wound feelings will not serve as objective criteria for wound healing (or in the contrary, wound discharge and dehiscence). A wound problem solely due to stitches and localized suture problems will not count as a wound problem. A keloid or altered pigment features will not be counted as a problem in this trial. Remission is defined as the absence of any problems and as the absence of any clinical signs of infection.

The primary outcome will be assessed on both, the Intention-to-treat and the per-protocol populations.

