### 11.3 Planned Analyses

All analyses will be performed for the entire study population. In a second step, all analyses will be separately performed according to subgroups of patients, based on the type of orthopaedic surgical procedure (e.g. arthroplasties, implant-related surgeries, etc.). We will use descriptive statistics and will perform group comparisons (using the Pearson- $\chi^2$ -test, the Fischer-exact-test, or the Wilcoxon-ranksum-test), as appropriate. We will also perform composite (SSI and wound problems) and separate (SSI or wound problems) multivariate analysis using a Cox regression model targeting the co-primary outcome variables. For the primary outcome parameter, univariable and multivariable results will be computed using a Cox regression analysis. Variables with a  $p$  value  $\leq 0.2$  in univariate analysis will be included in a stepwise forward selection process for multivariate analysis. Key variables will be checked for co-linearity and interaction. The number of variables in the final model is limited to the ratio of 1 variable to 5 to 8 outcome events. The significance level is  $p \leq 0.05$  (two-tailed).

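### The primary outcome is defined in conflicting ways (event, culture rule, time point, single or co-primary), so the same patient can be an event or a success, and the planned 10% vs 5% is not tied to one of them

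*Protocol*

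**What the plan says.** **Section 5, repeated in the synopsis outcome list.** One composite: "Remission (and inversely superficial or deep-space SSI and revision surgeries for non-infected wound problems; composite primary outcome) at 6 weeks", followed by an *and/or* that adds a 1-year time point for surgery with an implant. A surgical site infection (SSI) of any depth counts, whether or not it is re-operated.

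**Synopsis, Study Conduct.** "The primary study outcomes are unplanned revision surgery for SSI and wound problems at 42 days for all surgeries; or 1 year" for implant-related surgery. Here the event is an operation.

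**Section 9.1 (assessment of the primary outcome).** The outcome is judged visually as healed or delayed healing. Remission means no problems and no clinical signs of infection, and laboratory markers are not a criterion for wound healing. In doubtful cases "the opinion of the treating physician will dominate the decision upon the presence or absence of wound problems and/or infection". Sections 6.1 and 6.2.2 describe the trial as unblinded.

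**Section 3.2.1 (definitions).** An infection requires "microbiological evidence of bacteria in at least two intraoperative tissue samples" plus radiological and/or clinical evidence. A wound problem is one that leads to surgical revision. Remission takes laboratory signs into account and needs a minimum follow-up of one year with implants left in place "or two months for implant-free surgery".

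**Section 9.2.** The test-of-cure visit is at day 42 +/- 14 days. Only implant cases have a later follow-up, at 1 year +/- 2 months.

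**Section 11.3.** It plans composite and separate models, described as "multivariate analysis using a Cox regression model targeting the co-primary outcome variables", and its next sentence refers to one primary outcome parameter. The significance level is two-sided 0.05.

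**Sections 11.1 and 11.2.** The hypothesis attaches 10% vs 5% to surgical revisions. The sample size attaches the 10% to revision surgery and/or SSI. Neither gives a time point.

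**The concern.** These are statements within one protocol that cannot all be applied to the same patient, so this is not detail that a protocol may leave to an analysis plan. In an unblinded trial two things follow. First, the definition that is finally reported can be picked after the arm comparison is known. Second, the subjective parts of the outcome (delayed healing, doubtful infection) are decided by a treating physician who may know the allocation. The sample size is affected too: a control rate can only be checked, and power only defended, for a stated event over a stated period.

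**Working it through.** **1. Which patients change status**

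| Patient | Section 5 | Study Conduct | Section 3.2.1 | Section 9.1 |
|---|---|---|---|---|
| Superficial SSI, treated without surgery | event | no event (no revision) | not an infection (no intraoperative samples) | not in remission (clinical signs) |
| Delayed healing or dehiscence, not infected, no re-operation | no event | no event | no wound problem (no revision) | failure |
| Implant case, clean at 6 weeks, revised for infection at month 5 | success at 6 weeks, event at 1 year; *and/or* does not say which decides | event at 1 year | not in remission at 1 year | no time point given |
| Implant-free case, first infection signs at day 58 | after the 6-week time point | after day 42 | within the two-month minimum | no time point given |

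**2. Time point after implant-free surgery**

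The last scheduled window closes at 42 + 14 = day 56. Two months is about 61 days. The section 3.2.1 minimum therefore falls after the last planned contact with an implant-free patient.

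**3. The plan's sample size**

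Inputs (sections 11.2 and 11.3): p1 = 0.10, p2 = 0.05, d = 0.05, mean rate 0.075, two-sided alpha 0.05, power 80%, 1:1 allocation.

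- Without continuity correction: n = [1.960 × √(2 × 0.075 × 0.925) + 0.842 × √(0.10 × 0.90 + 0.05 × 0.95)]² / 0.05² = (0.7301 + 0.3121)² / 0.0025 = 434.4, so 435 per arm.
- With continuity correction: (434.4 / 4) × [1 + √(1 + 4 / (434.4 × 0.05))]² = 473.6, so 474 per arm.

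The stated 474 reproduces exactly.

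**4. Power at 500 per arm if the control rate differs**

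Power = Φ{[d − 1.960 × √(2 × p̄ × (1 − p̄) / n)] / √[(p1(1 − p1) + p2(1 − p2)) / n]}, with n = 500, p̄ the mean of the two rates, and no continuity correction. At 10% vs 5%: (0.05 − 0.03265) / 0.01658 = 1.046, giving 85%.

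The protocol gives no rate by definition, so every row except 10% is an assumption. The risk is halved throughout.

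| Control rate | Treated rate | Power |
|---|---|---|
| 12% | 6% | 91% |
| 10% | 5% | 85% |
| 9% | 4.5% | 81% |
| 8% | 4% | 76% |
| 7% | 3.5% | 70% |
| 5% | 2.5% | 55% |

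Power drops below 80% only when the control rate is under about 8.8%.

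**5. Error rate under a co-primary reading**

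Simulation under no effect, 500 per arm, assuming 5% SSI and 5% wound problems, mutually exclusive, each test at two-sided 0.05:

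- composite alone: 5%
- any of composite, SSI or wound problems significant: about 11%
- both components required: about 0.2%

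**The case against.** The best defence is that the formal outcome entry is the same in the synopsis list and in section 5, and that the departures are loose narrative. It is true that the synopsis as a whole does not contradict section 5; only its Study Conduct text does. But section 9.1 is the section that governs how the primary outcome is assessed, and section 3.2.1 gives the only infection definition for the trial, so neither can be set aside as narrative. Section 3.2.1 does speak of orthopedic infection and not of SSI by name, but no other definition of SSI is offered.

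Several stronger readings are tempting and are not supported:

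- **That 10% vs 5% belongs to no definition.** The wording in 11.2 is close to the section 5 composite, and that in 11.1 is close to Study Conduct. The figure has two labels; it is not without one.
- **That no implant-free patient can be declared in remission.** The two-month rule concerns remission of a former infection, and section 9.1 has its own remission definition with no minimum. An uninfected patient can meet 9.1 at day 42. What remains is one term with two definitions.
- **That the error rate is 11%.** This needs a rule that a win on any of three tests counts as success. The protocol states no such rule, and the singular in the next sentence of 11.3 points the other way.
- **That listing non-infection revisions as a secondary outcome is an error.** Reporting components of a composite as secondary is ordinary practice.
- **That a narrower definition necessarily misses 80% power.** At 9% it does not, and 11.1 assigns 10% to the narrower event itself.

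Separate horizons for implant and implant-free surgery are a legitimate choice and are not criticised here.

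**Conclusion.** The conflict is real and should be removed before any comparison of the arms, including the interim analysis. The protocol gives three versions of the event, an infection definition that excludes some of the events listed in section 5, time points that do not agree, and two descriptions of how many primary outcomes there are. The primary result is therefore not uniquely determined by the data.

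The sample-size arithmetic is correct. What is missing is the event and period to which the 10% refers. The possible cost in power depends on assumed rates: from 85% down to 55% if the control rate were 5%, or up to 91% if it were 12%. The multiplicity cost is conditional on a success rule that the plan does not contain.

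**What to change.** Use one definition in the synopsis, 3.2.1, 5, 9.1, 11.1, 11.2 and 11.3:

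1. **Event.** The section 5 composite: SSI of any depth, or unplanned revision for a non-infected wound problem.
2. **Test.** One primary test at two-sided 0.05. SSI alone and wound problems alone become secondary, and the term co-primary is deleted.
3. **Infection and healing criteria.** State that the two-sample rule in 3.2.1 does not decide superficial SSI. The investigators should then reconcile the SSI criteria and the 9.1 healing criterion with the composite.
4. **Horizon.** The 6-week assessment for implant-free episodes and the 1-year assessment for implant episodes, each with its existing window. Remove the two-month minimum and the *and/or* from the primary outcome. A hard cut at day 42 would not fit, because a patient may last be seen at day 28.
5. **Planning rates.** State the event and time point to which 10% vs 5% refers.

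The monitoring committee mentioned in 11.4 is not a suitable adjudicator of doubtful outcomes, because under 11.3.1 it acts on comparisons between the arms and decides on stopping.

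The cost is protocol wording, plus the investigators' work on the criteria. SSI alone can no longer be claimed as a primary result.

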### Secondary outcomes:

- Unplanned revision surgery for non-infection problems in same time period
- All adverse events during decolonization and hospitalization for surgery
- Subjective opinion on the decolonization (only for patients being decolonized)

## 6. STUDY DESIGN

### 6.1 General study design and justification of design

This is a prospective-randomized, controlled, unblinded, superiority trial, completed with a questionnaire of 5 key questions regarding the decolonization. We assess the following variables:

#### 6.1.2 In case of refusal or withdrawal from the study

When a patient refuses to take part in the study, or is rejected by the investigators, his/her treatment will continue according to usual therapeutic standards and follow-ups. If a patient's withdrawals his/her consent during the study period or up to one month after the last study visit, his/her information and results will be deleted from further analyses.

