#### 8.4 Data Collection and Follow-up for withdrawn participants

Withdrawn participants are instructed to continue surveillance according to the protocol and to contact the investigators if there are any questions or concerns that arise after completing the study.

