#### **9.1.4 Assessments in participants who prematurely stop the study**

Participants who prematurely stop the investigation are defined as patients who withdraw consent or who, in the opinion of the investigator, are no longer eligible to participate in the study. Where possible, such patients will complete an early-termination visit to undergo all assessments applicable to the corresponding (or next) scheduled study visit. For these patients, we will record eventual adverse events, physical examination, laboratory parameters, vital signs during a follow-up period determined by clinical control, which is usually up to one-year post intervention.

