### 10. SAFETY

#### 10.1 Decolonization Set

During the study, all serious adverse events (SAEs) are collected, fully investigated and documented in source documents and case report forms (CRF). Study duration encompasses the time from when the participant signs the informed consent until the last protocol-specific procedure has been completed, including a safety follow-up period. This is 42±14 days, or 1 year in case of an orthopaedic implant.

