#### 11.3.2 Final analyses

The intent-to-treat (ITT) population will consist of all randomized patients. Patients will be analysed according to treatment group assignment. Patient disposition and baseline characteristics will be based on the ITT population.

The per-protocol (PP) population will consist of all randomized patients who complete the study (or who are otherwise defined as a treatment failure) according to the clinical investigation plan and who have not deviated significantly from the protocol. All efficacy analyses will be repeated using the PP population. Any analysis involving microbiological assessments will exclude patients without an assigned baseline pathogen.

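### Section 6.1.2 drops from analysis every patient who withdraws consent, even after the primary outcome is recorded, which contradicts the ITT population in section 11.3.2

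*Protocol*

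**What the plan says.** Protocol section 6.1.2 deals with a patient who withdraws consent. If this happens "during the study period or up to one month after the last study visit, his/her information and results will be deleted from further analyses". The rule does not distinguish data gathered before withdrawal from data gathered after it, nor patients whose outcome is known from those whose outcome is not.

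Other sections treat the same patient differently:

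- **Analysis set.** Section 11.3.2: "The intent-to-treat (ITT) population will consist of all randomized patients", analysed by assigned group. Section 9.1: "The primary outcome will be assessed on both, the Intention-to-treat and the per-protocol populations".
- **Follow-up.** Section 8.4: "Withdrawn participants are instructed to continue surveillance according to the protocol". Section 9.1.4 expressly covers withdrawal of consent: "Participants who prematurely stop the investigation are defined as patients who withdraw consent", among others. It offers an early-termination visit and adds that "we will record eventual adverse events, physical examination, laboratory parameters, vital signs during a follow-up period determined by clinical control", usually up to one year. Section 9.2.5 repeats the early-termination visit.
- **Safety.** Section 10.1 has all serious adverse events collected and documented; section 10.1.3 has them reported to the sponsor-investigator within 24 hours.
- **Stopping the set.** Section 7.4 lets the investigator stop study treatment without taking the patient out of the study.

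Sections 6.1 and 6.2.2 state that the trial is unblinded. No section says how the removal rule and the ITT definition fit together.

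**The concern.** A patient cannot be both in a population of all randomized patients and removed from further analyses. Two analysts, one following section 6.1.2 and the other section 11.3.2, would build different primary datasets from the same trial.

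The timing makes this more than a labelling problem. For surgery without an implant the last visit is the test-of-cure visit at day 42 ± 14 days, and the removal window runs for another month. A patient revised for infection in week 5 who withdraws consent in week 9 can therefore leave the analysis with a recorded primary event. Patient and staff both know the allocation, and withdrawal may follow a bad result. If it does so more often in one arm, the analysed groups are no longer those that randomization created. The same removal would take that patient's adverse events out of the between-arm safety comparison, although safety is a stated objective.

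**Working it through.** **1. The passages side by side.** Take a randomized patient with a recorded primary event who withdraws consent within a month of the last visit.

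| Section | Consequence for this patient |
|---|---|
| 6.1.2 | Out of further analyses |
| 11.3.2 and 9.1 | In the ITT analysis of the primary outcome |
| 8.4, 9.1.4, 9.2.5 | Surveillance, early-termination visit and recording continue |
| 10.1, 10.1.3 | SAEs still documented and reported individually |

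The first two rows are a direct contradiction. The third is a tension: data are gathered that section 6.1.2 then keeps out of the analysis.

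**2. The plan's sample size.** Inputs from sections 11.2 and 11.3: event rates 10% and 5%, power 80%, two-sided alpha 0.05. With mean rate 0.075, the uncorrected size is

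n' = [1.960·√(2·0.075·0.925) + 0.842·√(0.10·0.90 + 0.05·0.95)]² / 0.05² = 434.4, rounded up to 435.

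With the continuity correction,

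n = (n'/4)·[1 + √(1 + 4/(n'·0.05))]² = 473.6, rounded up to 474.

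This reproduces the stated 474 per arm, which is not in dispute.

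**3. Power formula.** Let d be the difference in rates, s₀ the pooled and s₁ the unpooled standard error. The probability of rejection is

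Φ((d − 1.96·s₀)/s₁) + Φ((−d − 1.96·s₀)/s₁).

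At 500 per arm with 10% vs 5%: s₀ = 0.01666 and s₁ = 0.01658, so power is 85.2%. It is 83.3% at 474 per arm. The normal approximation is used without continuity correction, and each case is treated as one independent surgery episode.

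**4. Removal unrelated to outcome.** The protocol gives no withdrawal rate, so the fractions are assumptions.

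| Removed per arm | n per arm | Power |
|---|---|---|
| 0% | 500 | 85.2% |
| 2% | 490 | 84.5% |
| 5% | 475 | 83.4% |
| 10% | 450 | 81.4% |

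**5. Removal of event cases from one arm only.** This is a deliberate worst case: only patients with an event leave, and only in one arm. An arm with a 10% rate has 50 expected events. Removing k of them leaves a rate of (50 − k)/(500 − k).

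| k (share of 50 events) | Rate left in that arm | No true effect (10% both), removed from decolonization: type I error | True 10% vs 5%, removed from control: power |
|---|---|---|---|
| 0 | 10.0% | 5.0% | 85.2% |
| 5 (10%) | 45/495 = 9.1% | 7.8% | 71.4% |
| 10 (20%) | 40/490 = 8.2% | 17.1% | 52.0% |
| 15 (30%) | 35/485 = 7.2% | 34.3% | 30.7% |

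**6. Single datasets, uncorrected Pearson chi-square.**

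- Planned result: 50/500 vs 25/500 gives p = 0.0027. With 10 control events removed, 40/490 vs 25/500 (8.2% vs 5.0%) gives p = 0.0445.
- Borderline result: 50/500 vs 36/500 gives p = 0.114. With four decolonization events removed, 50/500 vs 32/496 gives p = 0.042.

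**The case against.** Several points on the other side are sound.

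- **Recording is not analysis.** Sections 8.4 and 9.1.4 concern surveillance and recording; section 6.1.2 concerns analysis. Data may be recorded for safety and left out of an efficacy analysis. This stands, so those sections are in tension with 6.1.2 rather than in strict contradiction. The contradiction with 11.3.2 and 9.1 remains.
- **Data and SAEs do not disappear.** A reader might infer that records are erased or serious events lost. The text does not support that: 6.1.2 speaks only of further analyses, and SAEs are still documented and reported. They can be missing only from the comparison between arms.
- **The primary outcome is not forgotten at withdrawal.** The list in 9.1.4 does not name infection or revision, so a reader might infer that they go uncollected. But the early-termination visit includes, where possible, all assessments of the corresponding or next visit, and sections 9.2.3 and 9.2.4 include recording infection.
- **A skin reaction need not lead to removal.** Under section 7.4 the set can be stopped while the patient stays in the study. Reactions to the set would also arise mainly before surgery or within two days after it, before infection status is known. Such withdrawals may differ by arm but do not follow the outcome.
- **The figures in step 5 are extreme.** Section 9.2.3 expects no major drop-out because visits are routine care, and removal unrelated to outcome costs little.
- **Retention may be restricted.** What may be kept after withdrawal depends on the signed consent and on the law, to which section 12.6 refers.

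The conflict cannot be set aside as detail for a statistical analysis plan, because the protocol states two rules that cannot both be followed. Nor does section 11.4 resolve it: that section concerns missing data and major deviations, whereas here the outcome may be recorded and the patient compliant.

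**Conclusion.** The point holds as a contradiction between section 6.1.2 and sections 11.3.2 and 9.1, with a secondary tension against 8.4, 9.1.4 and 9.2.5. In an unblinded trial, a rule that allows removal after the outcome is known can bias the comparison in either direction.

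The size cannot be determined from the protocol. It ranges from slight, if withdrawal is unrelated to outcome, to serious, if event cases leave from one arm only. The latter range rests wholly on assumed one-sided withdrawal. A reader might infer that the primary result is bound to be biased; the documents do not support that, since they give no reason to expect many withdrawals. Should be fixed: the rule is wrong and cheap to correct, but its harm is possible rather than shown.

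**What to change.** 1. Replace the removal rule in section 6.1.2. Data collected up to the date consent is withdrawn stay in the ITT and safety analyses under the assigned arm, as far as the signed consent and applicable law allow. No new study data are collected after that date without consent.
2. Align sections 8.4, 9.1.4, 9.2.5 and 11.3.2 with this rule, and refer to the existing provision in 7.4 for stopping the set without leaving the study. If consent or law requires some data to be left out, say so in 11.3.2 as a named exception to the ITT definition.
3. Put the same rule in the information sheet, because what patients sign governs what may be kept.
4. Report withdrawals of consent by arm, with event status where known.

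The cost is an amendment to the protocol and information sheet. It probably counts as substantial under section 2.10 because it touches participants' rights, so ethics committee approval would come first. The sample size does not change, and no extra patients, visits or staff are needed.
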